## Abstract

**Background:**

An effective diagnostic work-up in hospitalized patients with acute ischemic stroke is vital to optimize secondary stroke prevention. The *HEart and BRain interfaces in Acute ischemic Stroke* (HEBRAS) study aims to assess whether an enhanced MRI set-up and a prolonged Holter-ECG monitoring yields a higher rate of pathologic findings as compared to diagnostic procedures recommended by guidelines (including stroke unit monitoring for at least 24 h, echocardiography and ultrasound of brain-supplying arteries).

**Methods/Design:**

Prospective observational single-center study in 475 patients with acute ischemic stroke and without known atrial fibrillation. Patients will receive routine diagnostic care in hospital as wells as brain MRI, cardiac MRI, MR angiography of the brain-supplying arteries and Holter-monitoring for up to 10 days. Study patients will be followed up for cardiovascular outcomes at 3 and 12 months after enrolment.

**Discussion:**

By comparing the results of routine diagnostic care to the study-specific MRI/ECG approach, the primary outcome of HEBRAS is the proportion of stroke patients with pathologic diagnostic findings. Predefined secondary outcomes are the association of stroke localization, autonomic dysbalance and cardiac dysfunction as well as the effect of impaired heart-rate-variability on long-term clinical outcome.

The investigator-initiated HEBRAS study will assess whether an enhanced MRI approach and a prolonged ECG monitoring yield a higher rate of pathological findings than current standard diagnostic care to determine stroke etiology. These findings might influence current diagnostic recommendations after acute ischemic stroke. Moreover, HEBRAS will determine the extent and clinical impact of stroke-induced cardiac damage.

**Trial registration:**

Clinicaltrials.gov NCT02142413.

## Background

Variations and delays in the diagnostic procedures during hospitalization after acute ischemic stroke are common [1–3]. At the same time, stroke etiology remains cryptogenic in about 20–25 % of stroke unit patients [4].

Recent studies have shown that magnetic resonance imaging (MRI) and MR angiography are able to detect cardiac [5, 6], aortic [7] as well as carotid sources of embolism with comparable sensitivity as compared to diagnostic ultrasound [8]. Moreover, prolonged ECG monitoring can significantly increase the detection rate of atrial fibrillation (AF) [9, 10]. The detection of AF implies a four- to fivefold increased risk of stroke [11]. These developments may allow for a more effective diagnostic work-up in patients with acute ischemic stroke as compared to standard diagnostic procedures, namely ultrasound of the brain-supplying arteries, echocardiography and stroke unit monitoring. However, there is no common standard of stroke unit monitoring [12] and guidelines [13] do not strictly recommend prolonged ECG monitoring [14]. In addition, availability of echocardiography is often limited [1, 15], and a substantial number of stroke patients are not willing or able to undergo semi-invasive transesophageal echocardiography, while transthoracic echocardiography is not sufficient for assessing aortic plaque and left atrial thrombi.

The prospective observational *HEart and BRain interfaces in Acute ischemic Stroke* (HEBRAS) study therefore aims to assess the detection rate of pathologic findings relevant to stroke etiology as obtained by an enhanced MRI set-up (including brain MRI, cardiac MRI, MR angiography of the brain-supplying arteries) and a prolonged, non-invasive, commonly available Holter monitoring (of up to 10 days duration) in comparison to findings obtained by routine diagnostic procedures after acute stroke. In addition, the underlying pathophysiological mechanisms and the prognostic impact of stroke-induced cardiac damage are still poorly understood [16, 17]. For that reason, the investigator-initiated HEBRAS study attempts to shed more light on the relationship between stroke localization (e.g., insular involvement), observed cardiac damage (as indicated by troponin elevation) and the activation of the autonomic nervous system (as indicated by impairment of heart rate variability and elevated urinary norepinephrine levels). Moreover, stroke-induced autonomic dysfunction and observed cardiac damage will be analyzed with respect to functional outcome, mortality, recurrent stroke and myocardial infarction during a one year follow-up.

## Methods

### Study design

The Center for Stroke Research Berlin (CSB) is the sponsor of the investigator initiated HEBRAS study, which is supported by a grant from the German Federal Ministry of Education. The study was approved by the scientific advisory board of the CSB in September 2013, and by the Ethics Committee of the Charité - Universitätsmedizin Berlin, Germany (EA2/033/14) in March 2014. All study procedures are carried out in accordance with the principles of Good Clinical Practice and the Declaration of Helsinki. All study patients have to fulfill the study entry criteria listed in Table 1 including written informed consent.

**Table 1 Tab1:** Inclusion and exclusion criteria of the HEBRAS study

Inclusion criteria
• Written informed consent by patient
• Age ≥ 18 years.
• Acute ischemic stroke (with matching brain lesion on MR imaging).
• Admission to the stroke unit at the Charité, Campus Benjamin Franklin
• Enrolment within 144 h after onset of stroke-related symptoms.
Exclusion criteria
• Known AF by past medical history before hospital admission.
• AF according to 12-lead ECG on hospital admission.
• AF according to inpatient ECG recording / stroke unit monitoring before enrolment.
• Pre-stroke life expectancy less than 1 year.
• Participation in an interventional study.
• Pregnancy and / or breast-feeding.
• Contraindications to undergo MRI (i.e., mechanic heart valve, cardiac pacemaker)
• History of adverse response to MRI contrast agents
• Clinically severe heart failure (NYHA III-IV) [37]
• Renal insufficiency (creatinine > 1.3 mg/dl (females); creatinine > 1,7 mg/dl (males))

Study patients will receive routine diagnostic procedures in hospital (defined as stroke unit monitoring (according to clinical needs), echocardiography, ultrasound of the brain-supplying arteries, and 24-hour Holter-ECG (if indicated according to the treating physician)). Moreover, study patients will undergo an enhanced MRI work-up (comprising brain as well as cardiac MRI, MR angiography of the aortic arc and the supra-aortic, brain-supplying arteries) combined with Holter-ECG of up to 10 days (including a maximum of 5 days after hospital discharge). For the primary outcome, the results of routine diagnostic care will be compared to study-related diagnostics. Results of the ECG core lab analysis will be provided to study patients and treating physicians. Study patients will be followed up for cardiovascular outcomes e.g., recurrent stroke, major vascular events, death and degree of dependency at 3 and 12 months after enrollment.

### Stroke etiology

Etiology will be determined according to TOAST [18] and ESUS criteria [4]. The following diagnostic findings will be regarded as pathologic and relevant to stroke etiology: atrial fibrillation of any type, sick sinus syndrome, bacterial or nonbacterial thrombotic endocarditis, ipsilateral carotid or intracranial stenosis of ≥ 50 % according to NASCET [19], left atrial or left ventricular thrombus, atrial myxoma, acute myocardial infarction resulting in wall motion abnormalities, akinetic left ventricular segment, dilated cardiomyopathy, systolic dysfunction with reduced left ventricular ejection fraction (<45 %), aortic plaque of ≥ 4 mm.

### Magnetic resonance imaging

In HEBRAS, enhanced diagnostic MRI work-up is defined as brain MRI, cardiac MRI and MR-angiography of the aortic arc and the brain-supplying arteries. All MR examinations are performed on a 3 Tesla MR scanner (TIM TRIO, Siemens, Erlangen, Germany). Cerebral MRI mainly consists of a T2*-sensitive sequence (TR 620 ms, TE 20 ms, flip angle 20°, FOV 220 mm, slice thickness 5 mm) to exclude intracerebral hemorrhage, a diffusion weighted (DWI) sequence (TR 7600 ms, TE 93 ms, FOV 230 mm, slice thickness 2.5 mm) for detection of ischemic tissue, and a 3D time-of-flight (TOF) angiographic sequence (TR 22 ms, TE 3.86 ms, flip angle 18°, FOV 200 mm, slice thickness 0.65 mm) for imaging of intracranial vessels. For cardiac imaging, initially a dark-blood–prepared HASTE (half-Fourier acquisition single-shot turbo spin-echo) sequence (TR 750 ms, TE 49 ms, Flip angle 160°, Slice thickness 5 mm) is acquired, followed by 2 chamber as well as 4 chamber view acquisitions using a cine SSFP sequence (TR 40.56 ms, TE 1.48 ms, flip angle 50°, slice thickness 5 mm) with prior scouting for individual frequency adjustment. Post-contrast imaging is performed after intravenous injection of 0.1 mmol/kg body weight Gadobutrol (Gadovist®, Bayer Schering Pharma, Berlin, Germany) with post-contrast cine imaging parameters held constant. For angiographic imaging of the aortic arch as well as extracranial cerebral arteries, a three-dimensional TWIST (Time-resolved angiography With Interleaved Stochastic Trajectories) sequence was used (TR 2.36 ms, TE 0.99 ms, Flip angle 20°, Slice thickness 1.40 mm). Finally, myocardial late enhancement is characterised employing a turbo FLASH (Fast Low Angle SHot) sequence (TR 750.00 ms, TE 1.97 ms, Flip angle 20°, Slice thickness 8 mm).

The following stratification of lesion localization is planned: left / right anterior cerebral artery, left / right middle cerebral artery, left / right posterior cerebral artery, left / right anterior choroideal artery, left / right insular cortex, left / right basal ganglia, left / right thalamus, left / right cerebellum, left / right brainstem, left / right medulla oblongata.

To bypass restrictive *a priori* assumptions on a specific relationship between stroke lesion and laboratory changes, an additional voxel-by-voxel analysis of lesion location and troponin-elevation will be conducted employing statistical principles developed for functional brain imaging [20, 21].

### Study ECG & core lab analysis

Additional ECG recording will be performed by using the portable CardioMem®4000 (GETEMED AG, Teltow, Germany). Study ECG will be started as soon as possible after enrolment and will be continued for a maximum of 10 days, i.e., two consecutive ECG measurements of five days. When patients are discharged before the first five days are completed, ECG recorder will be changed at discharge, resulting in an overall duration of less than ten days in Holter-ECG.

Study ECG data will be transmitted to the cardiac core lab at Department of Cardiology and Pneumology, Georg-August-University Göttingen, Germany for analysis. Raters analysing ECG-data will be blinded for clinical data including infarct localization. Core lab analysis will be provided to the respective study patient and the patient’s treating physician (if indicated by clinical assumption).

The following definitions will be used throughout the study: Atrial fibrillation: Absolute arrhythmia lasting ≥ 30 s as defined in the current ESC guideline [22]. Short atrial tachycardia: Atrial tachycardia lasting < 30 s and consisting of ≥ 6 conducted premature activations. Excessive supraventricular ectopic activity: More than three premature atrial complexes per hour [23]. Atrial flutter will be reported separately, and the study specifies to initiate anticoagulation for atrial flutter in the same way as for AF. The analysis will include: heart rhythm; PQ intervall [s], minimal [bpm], maximal [bpm] and mean heart rate (HR) [bpm], and measures of Heart rate variability (HRV) such as the standard deviation of beat-to-beat (NN) intervals (SD-NN), Root Mean Square of Successive Differences (rMSSD), HRV-Triangular Index (HRV-TI), low and high frequency (LF and HF, respectively) band and LF/HF Index [24].

### Baseline visit in hospital

Baseline assessment of all study patients will include: a detailed analysis of patient demographics (also including time of stroke onset, hospital admission as well as admittance to the ward), clinical characteristics (including the National Institutes of Health Scale Score [25] and the modified Rankin Scale score [26], vital signs, medical history and concomitant diseases, extend and results of inpatient ECG recording, laboratory results (all data of clinical routine assessment plus high-sensitivity (hs) troponin and NT-proBNP), results of imaging (head CT/MRI, carotid ultrasound of brain-supplying arteries, echocardiography) and TOAST classification at hospital discharge (before evaluation of the additional ECG monitoring), in hospital treatment (i.e., thrombolysis, ventilation etc.) as well as in hospital complications (such as pneumonia, recurrent stroke or myocardial infarction).

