### Statistical analysis

The sample size calculation is based on the aforementioned primary hypothesis (Table 2), that an enhanced diagnostic work-up consisting of cerebral and cardiac MRI (including contrast-enhanced angiography of the aortic arch and the carotid arteries) combined with a prolonged ECG-Monitoring (of up to 10 days duration) leads to a reduction in the number of strokes classified as cryptogenic from 30 to 25 % when compared to the routine diagnostic work-up at the Stroke Unit. A sample size of 396 patients which receive both the enhanced as well as the routine diagnostic work-up would provide a power of 79 % to detect a difference in the number of strokes classified as cryptogenic (from 30 % after routine diagnostic work-up to 25 % after enhanced diagnostic work-up, and with assumed 13 % discordant pairs: 9 % diagnosed as cryptogenic stroke by routine work-up but not according to enhanced diagnostic work-up, and 4 % diagnosed as cryptogenic stroke by enhanced work-up but not according to routine diagnostic work-up). The hypothesis will be tested using the McNemar-Test (two-sided, α = 0.05). An interim analysis (with a significance level of α1 = 0.004) will be performed when 264 patients (67 %) are enrolled in the study. If p is ≤ α1 at the interim analysis, the study will be terminated. When the study will be continued, the primary endpoint will be tested with α2 = 0.046 (two- tailed); the overall significance level will be 5 %.  Taking into account a drop-out rate of about 20 %, 475 patients will have to be enrolled in the study. 

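### The routine aetiology label is separated from the study ECG but not from the study cardiac MRI and MR angiography, so the comparator of the primary paired test is not protected from half of the enhanced work-up

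*Protocol article*

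**What the plan says.** **Comparison.** Study design in the Protocol article states: "For the primary outcome, the results of routine diagnostic care will be compared to study-related diagnostics". Statistical analysis makes this a McNemar test on cryptogenic classification: 30 % after routine and 25 % after enhanced work-up. One discordant cell is "9 % diagnosed as cryptogenic stroke by routine work-up but not according to enhanced diagnostic work-up"; the opposite cell is 4 %.

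**The two sides.** Routine work-up is "defined as stroke unit monitoring (according to clinical needs), echocardiography, ultrasound of the brain-supplying arteries, and 24-hour Holter-ECG" (the last if indicated). It contains no MRI. On the other side, "enhanced diagnostic MRI work-up is defined as brain MRI, cardiac MRI and MR-angiography of the aortic arc and the brain-supplying arteries", to which the prolonged Holter is added.

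**The label and its timing.** Stroke etiology says that cause is determined by TOAST and ESUS criteria. Baseline visit in hospital records "TOAST classification at hospital discharge (before evaluation of the additional ECG monitoring"), alongside "results of imaging (head CT/MRI, carotid ultrasound of brain-supplying arteries, echocardiography"). Table 3 marks cardiac MRI, MR angiography and brain MRI in the Day 1 column, before Discharge.

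**Blinding and feedback.** The only stated blinding is that of the ECG raters to clinical data. The only stated feedback is of the study ECG: "Results of the ECG core lab analysis will be provided to study patients and treating physicians". On who sees the study MRI, and when, the article is silent.

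**The concern.** A paired comparison of two work-ups needs each label to rest on its own tests. The authors evidently saw this, because they wrote a rule that keeps the discharge classification apart from a study test. The rule covers one of the two study tests. The other is scheduled earlier, in the same hospital stay, before the label is assigned.

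Two routes are open if discharge TOAST is the routine side. A thrombus, stenosis or aortic plaque seen only on study MRI may be known to whoever assigns the class. It may also prompt a confirmatory echocardiogram or ultrasound, which is then recorded as a routine detection. Either route turns a pair that should count for the enhanced work-up into a concordant pair. The design rests on a difference of 5 percentage points, so a small number of such pairs matters. A label assigned with knowledge of the MRI cannot be fully repaired at the analysis stage.

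**Working it through.** **1. Reproduce the planned power.** Inputs from Statistical analysis: n = 396, p10 = 0.09 (cryptogenic by routine only), p01 = 0.04 (cryptogenic by enhanced only), two-sided alpha 0.05. With d = p10 − p01 and s = p10 + p01, the normal approximation is

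power = Φ[(d√n − z·√s) / √(s − d²)], z = 1.960, √396 = 19.900.

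Here d = 0.05 and s = 0.13:

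(0.05 × 19.900 − 1.960 × √0.13) / √(0.13 − 0.0025) = (0.9950 − 0.7067) / 0.3571 = 0.807, and Φ(0.807) = 0.790.

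The stated 79 % is reproduced. At the final-analysis level of 0.046 the same formula gives 78.0 %. No figure in the plan is disputed.

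**2. Leakage from the 9 % cell.** Suppose x percentage points of the 9 % cell are findings made only by study MRI that reach the routine label. Those pairs become concordant: p10 = 0.09 − x/100, with p01 held at 0.04. The article gives no value for x and does not divide the 9 % between MRI and prolonged ECG. The range 0 to 3 is therefore an assumption. One point is about four patients (396 × 0.01 = 3.96).

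| x (points) | Routine cryptogenic | d | s | Numerator | Denominator | Ratio | Power |
|---|---|---|---|---|---|---|---|
| 0 | 30 % | 0.05 | 0.13 | 0.9950 − 0.7067 | 0.3571 | 0.807 | 79 % |
| 1 | 29 % | 0.04 | 0.12 | 0.7960 − 0.6790 | 0.3441 | 0.340 | 63 % |
| 2 | 28 % | 0.03 | 0.11 | 0.5970 − 0.6500 | 0.3303 | −0.161 | 44 % |
| 3 | 27 % | 0.02 | 0.10 | 0.3980 − 0.6198 | 0.3156 | −0.703 | 24 % |

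**3. Leakage in both cells.** Knowledge of the MRI could also overturn a routine finding that the enhanced work-up does not confirm, which would shrink the 4 % cell. If both cells lose the same share, the loss of power is smaller:

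- 25 % of each: p10 = 0.0675, p01 = 0.03, d = 0.0375, power 67 %.
- 50 % of each: p10 = 0.045, p01 = 0.02, d = 0.025, power 50 %.

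**4. Direction.** Steps 2 and 3 both move the difference toward zero. The opposite is possible. If a known MRI result led to a routine test being left out, a finding that routine care would have made is lost, the routine cryptogenic share rises and the difference widens.

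**The case against.** The strongest reply is that nothing here is shown to happen. The discharge TOAST is listed among baseline variables and is nowhere named as the routine side of the McNemar table. Study design and Study outcomes speak of the results or findings of each work-up, and the routine definition excludes MRI. On that reading, a plaque seen only on study MRI is not a routine finding. The imaging recorded next to TOAST omits cardiac MRI and MR angiography. Feedback to physicians is stated only for the ECG, which may be why the timing rule mentions only the ECG. A condensed article may also leave reader blinding and feedback to the full protocol.

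Much of this stands, and it rules out several stronger readings that a reader might infer:

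- That MRI findings do leak into the comparator. The article does not say that cardiac MRI or MR angiography results reach the person who assigns TOAST.
- That discharge TOAST is the stated comparator. It is only the sole routine classification described.
- That the bias must be toward zero. Step 4 of the working shows a route the other way.
- That brain MRI is itself a leak. Entry requires "Acute ischemic stroke (with matching brain lesion on MR imaging"), so a brain MRI is known clinically in every patient.
- That 63 %, 44 % and 24 % measure the harm. They illustrate an assumed share. If most of the 9 % is atrial fibrillation found on the Holter, x could be close to 0.

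The reply does not remove the point. The article is not merely silent: it states a separation rule, and that rule covers one of the two study tests. The McNemar test needs a routine cryptogenic label, and the only candidate described is not kept apart from the MRI. Following the text as written permits the leak.

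**Conclusion.** The point holds in conditional form. The routine label, as far as the article describes it, is protected from the study ECG and not from the study cardiac MRI and MR angiography performed before it is assigned. If that label is the routine side of the primary test, the paired difference can be biased, most likely toward zero. Under the assumed range of 0 to 3 points, the expected difference falls from 5 to 2 points and power from 79 % to 24 %. The actual size cannot be obtained from the document. The conclusion rests on two assumptions: that discharge TOAST, or a label formed in the same way, serves as the comparator, and that the full protocol contains no wider separation rule. If it does contain one, the article needs only to say so.

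**What to change.** - Name the classification that forms the routine side of the McNemar table.
- Assign it by a fixed rule from the routine tests listed under Study design plus the clinical brain imaging needed for entry, without study cardiac MRI, MR angiography or study ECG results. The study's cerebral MRI includes an intracranial time-of-flight sequence and intracranial stenosis is a qualifying finding, so the rule should say on which side that sequence counts.
- Flag each routine test ordered because of a study finding. Do not count these as routine detections in the primary analysis, or at the least exclude them in a sensitivity analysis.
- Keep TOAST at discharge as a descriptive variable.

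None of this requires study MRI results to be withheld from clinicians, because a rule applied to recorded routine fields does not depend on what the treating team knows. The cost is a test-level flag on the case report form for source and reason for ordering, and a little more analysis work. The routine results themselves are already collected at the baseline visit. The rule cannot restore routine tests that were never done because an MRI result was known, so that limitation should be stated.

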### Study follow-up

Follow-up will be done 3 months and one year after the index stroke by a telephone interview conducted by trained personal of the Center for Stroke Research Berlin, Germany. The following data will be assessed: medication, recurrent ischemic stroke and other major vascular events, major bleeds, and the mRS score. Additionally, (all-cause) death and date of death will be registered using information from registration offices.

### Study outcomes

The primary outcome of the HEBRAS study is the rate of pathologic findings relevant to stroke etiology in patients with acute ischemic stroke obtained by enhanced diagnostic MRI work-up combined with prolonged Holter-monitoring in comparison to findings obtained by the routine diagnostic work-up in this cohort of patients. The primary hypothesis is that the detection rate of pathologic findings can be increased by undergoing enhanced diagnostic MRI work-up combined with prolonged Holter-monitoring. The primary outcome and all secondary outcomes are listed in Table 2, and a flowchart of study specific data acquisition is provided in Table 3.

**Table 2 Tab2:** Primary outcome and secondary outcomes of the HEBRAS study

Primary outcome
• Detection rate of pathologic findings relevant to stroke etiology in patients with acute ischemic stroke obtained by enhanced diagnostic MRI work-up combined with prolonged Holter-monitoring in comparison to findings obtained by routine diagnostic work-up.
Secondary outcomes
• To assess the benefit of prolonged continuous ECG-monitoring in AIS patients to detect paroxysmal AF.
• To determine the proportion of patients with first detected paroxysmal AF by prolonged Holter-monitoring (for up to 5 days) after hospital discharge.
• To identify the impact of stroke localization on autonomic changes (as indicated by elevated urinary norepinephrine levels and measures of HRV) or cardiac dysfunction (as indicated by troponin T serum levels).
• To identify the impact of impaired HRV on recurrent vascular events and clinical outcome after AIS at 3 or 12 months after the index stroke, respectively.
• To assess the predictive value of imaging and biomarkers for AF-detection in patients with acute ischemic stroke.

**Table 3 Tab3:** Study flowchart of the HEBRAS study

	In-hospital stay				Follow-up	
	Admission	Day 1	Day ≥2	Discharge	3 months	12 months
Baseline data*	X					
Past medical history	X				X	X
Heart rate at rest (routine)	X	X	Daily	X		
Heart rhythm (routine)	X	X	Daily	X		
12-lead ECG	X					
24-hour Holter			(X)			
Additional ECG monitoring^a^	ongoing			ongoing^c^		
Respiratory rate	X	X	Daily			
Clinical signs of infection	X		X	X		
Leukocytes [per mm^3^]	X					
Creatinine [mg/dl]	X					
Potassium [mmol/l]	X					
Serum hs troponin I [ng/l]	X	X				
NT-proBNP [ng/l]		X				
Urine norepinephrine [nmol/l]		X				
Cardiac MRI		X				
MR angiography^b^		X				
Brain MRI		X				
NIHSS	X			X		
Modified Rankin scale score	X			X	X	X
Recurrent stroke, myocardial infarction or death of any cause			X	X	X	

^a^see Methods section for more details

^b^including the aortic arc and brain supplying arteries

^c^extended for up to 5 days after hospital discharge/ transfer to a rehabilitation clinic

